Distinguishing these forms of racial bias is important because they are associated with different aspects of healthcare. A recent review [23] provides evidence that providers’ greater implicit prejudice is associated with poorer quality patient-provider communication during racially discordant interactions, [24–28] which can further result in less patient satisfaction and trust in providers (Fig. 1) [29–31]. There is strong evidence that providers’ greater explicit negative stereotyping of Black patients is associated with suboptimal clinical recommendations for Black patients [21, 32, 33]. Drawing on findings from prior research, we developed a conceptual model highlighting genetic counselor bias, particularly implicit prejudice and explicit stereotyping, as major factors contributing to racial disparities in the genetic counseling process. We propose that patient-provider communication will be poorer for Black patients than for White patients (Path A) and that genetic counselors’ implicit prejudice toward Black people is negatively associated with the quality of patient-provider communication for Black patients, but not for White patients (Path C). We also propose that the content of clinical discussions will be lower in quality for Black patients than for White patients (Path B), and genetic counselors’ explicit negative stereotypes about Black people are negatively associated with the quality of clinical discussions for Black patients, but not for White patients (Path D). Finally, lower quality patient-provider communication and clinical discussions, in turn, will lead to Black patients’ negative perception of counselors and genetic counseling encounters (Paths E & F), ultimately contributing to racial disparities in patient-centered outcomes (Path G).

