## Methods

The overarching goal of this research is to compare and contrast the nature of cancer genetic counseling encounters and patient-centered outcomes between Black and White patients in the naturalistic clinical setting. We will test our hypotheses by addressing four specific aims: **Aim 1**) To compare/contrast the nature of patient-provider communication by patient race (Black vs. White); **Aim 2**) To compare/contrast the clinical discussion content by patient race; **Aim 3**) To quantify the role of each type of counselor bias in patient-provider communication (Aim 1) and clinical discussion content (Aim 2); and **Aim 4)** To quantify the role of patient-provider communication and clinical discussion content with patient-centered outcomes (trust, satisfaction, therapeutic alliance, empowerment, genetic testing completion). These aims will be achieved through an observational study with a convergent mixed methods research design. Table 1 provides an overview of the study design.

**Table 1 Tab1:** An overview of the study designs

Aims	Data sources	Analyses	Goals
1	• Recorded encounters	Quantitative analyses of provider communication style and the overall quality of patient-provider communication Qualitative analyses of transcribed encounters for the four basic interaction structures	Identify specific aspects of patient-provider communication during cancer genetic counseling encounters that are different between Black and White patients
2	• Recorded encounters	Qualitative analyses of transcribed encounters for (1) the presence/absence of the key topics for risk communication and genetic test consent during cancer genetic counseling encounters that were identified by NCI; and (2) additional topics discussed during cancer genetic counseling encounters	Identify specific clinical discussion topics during cancer genetic counseling encounters that are different between Black and White patients
3	• Provider baseline survey • Patient baseline survey • Coded encounters	Quantitative analyses of associations between the four forms of provider bias and (1) patient-provider communication as well as (2) clinical discussion content that were identified in Aims 1 & 2	Identify specific aspects of patient-provider communication/clinical discussion topics that contribute to racial disparities in the cancer genetic counseling process and reflect provider bias

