4	• Provider baseline survey • Patient baseline survey • Provider post-encounter survey • Patient post-encounter survey • Coded encounters	Quantitative analyses of associations between (1) patient-provider communication as well as (2) clinical discussion content that were identified in Aims 1 & 2	Identify specific aspects of patient-provider communication/clinical discussion topics that contribute to racial disparities in the cancer genetic counseling process and in patient-centered outcomes

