Continuous: Likert scale	*Patient-provider communication* (Provider communication style; The overall quality of patient-provider communication)	Linear regression with GEE
Continuous: Frequency	*Patient-provider communication* (Each type of silence; Each type of adjacency pairs; Each type of problems)	Poisson regression with GEE
Continuous: Proportion	*Patient-provider communication* (Topics initiated by providers; Primary units allocated to providers; Silence followed by provider talks; Repairs initiated by providers; Problems repaired by providers)	Linear regression with GEE
Continuous: Duration	*Patient-provider commu*nication (Each type of silence) *Clinical discussion con*tent (The amount of time spent on discussing a given topic)	Linear regression with GEE
Dichotomy	*Clinical discussion content* (The presence/absence of a given discussion topic)	Logistic regression with GEE
Multiple categories	*Patient-provider communication* (The primary units of turns)	Multinomial logistic regression with GEE

Finally, Aim 4 (to quantify the impact of patient-provider communication/clinical discussion content with patient-centered outcomes) examines Paths E and F in our conceptual model. The analyses will be carried out in steps similar to those in Aim 3. In Step 1, we will identify covariates associated with patient-centered outcomes by computing correlations among all aspects of patient-provider communication/clinical discussion topics and factors assessed in the patient baseline survey, the provider baseline survey, and the provider post-encounter survey. In Step 2, we will compute partial correlations between all aspects of patient-provider communication/clinical discussion topics identified in Aims 1 and 2 and patient-centered outcomes while controlling for covariates identified in Step 1. In Step 3, we will conduct a linear regression with GEE and Bonferroni correction for each self-reported outcome (e.g., trust, satisfaction, therapeutic alliance) and a logistic regression with GEE for behavioral outcome (genetic testing completion). All regressions will include the same set of predictors (aspects of patient-provider communication/clinical discussion topics that remain significant in Step 2, and care modality) and covariates. Aspects of patient-provider communication/clinical discussion topics that remain significant in Step 3 are considered as potentially important intervention points for reducing racial disparities in patient-centered outcomes.

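### No stated model estimates the Black-White difference in any patient-centered outcome, although the goal and the Aim 4 conclusion both refer to it

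*Protocol article*

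**What the plan says.** All references are to the protocol article.

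- **Goal (Methods, opening paragraph).** The overarching goal is "to compare and contrast the nature of cancer genetic counseling encounters and patient-centered outcomes between Black and White patients in the naturalistic clinical setting".
- **Conceptual model (Background).** Poorer communication and discussion lead to negative perceptions among Black patients, "ultimately contributing to racial disparities in patient-centered outcomes (Path G").
- **Table 1, goal for Aim 4.** Identify the aspects and topics that "contribute to racial disparities in the cancer genetic counseling process and in patient-centered outcomes".
- **Statistical analysis, Aim 4.** The aim "examines Paths E and F in our conceptual model". In Step 1, "we will identify covariates associated with patient-centered outcomes by computing correlations among all aspects of patient-provider communication/clinical discussion topics and factors" from the baseline surveys and the provider post-encounter survey. The Step 3 regressions of trust, satisfaction, alliance and testing completion share one predictor set, "aspects of patient-provider communication/clinical discussion topics that remain significant in Step 2, and care modality", plus covariates.
- **Aim 4 conclusion.** Aspects still significant after Step 3 "are considered as potentially important intervention points for reducing racial disparities in patient-centered outcomes".

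**The concern.** The goal and the conclusion are both about a difference between Black and White patients in what patients experience and do after counseling. A reader would expect one model per outcome that estimates this difference, and a second that shows what happens to it when communication and discussion content are added. Neither is specified.

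At stake is how Aim 4 can be read. Its results would be presented as targets for reducing a disparity whose size, direction and even presence in this sample had not been estimated. The Discussion section intends to build interventions on them, including lists of topics to cover and topics that could be dropped.

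**Working it through.** **1. Which model has race, and which has patient outcomes**

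| Aim | Paths assigned | Outcomes modelled | Patient race a named predictor? |
|---|---|---|---|
| 1 | A | Affect ratings, overall quality, linguistic patterns | Yes, with race by modality |
| 2 | B | Discussion topics (yes/no, time) | Yes, with race by modality |
| 3 | C, D | Communication aspects and topics | Yes, with interactions up to four-way |
| 4 | E, F | Trust, satisfaction, alliance, empowerment, testing completion | No |

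No row has both race as a named predictor and a patient outcome as the dependent variable. Path G is assigned to no aim.

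**2. Could race enter Aim 4 as a covariate?**

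Yes. Race is a patient baseline-survey item, so Step 1 may pick it up. Two things limit this. Entry depends on a data-driven screen, and as worded that screen correlates survey factors with communication aspects and topics, although its declared purpose is to find covariates of the outcomes. And in Step 3 race would stand beside the aspects, which the Discussion section describes as mediators.

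An illustration with assumed coefficients (race coded 0/1, unit-variance errors) shows why that position matters. Let race to aspect be −0.5 and aspect to outcome be 0.5, with no direct race effect.

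- Total race difference: −0.5 × 0.5 = −0.25 (simulated −0.246).
- Race coefficient with the aspect in the model: 0 (simulated 0.005).

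The adjusted coefficient is what remains after the aspect, not the disparity.

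**3. Does a significant aspect imply a disparity in the outcome?**

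Not necessarily. Keep the same coefficients and add an assumed direct race effect of +0.25.

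- Total race difference: −0.25 + 0.25 = 0 (simulated −0.001).
- Slope of the aspect in a model without race: 0.5 + 0.25 × cov(race, aspect)/var(aspect). With equal groups, cov = −0.5 × 0.25 = −0.125 and var = 1 + 0.5² × 0.25 = 1.0625, so the slope is 0.5 − 0.25 × 0.125/1.0625 = 0.47 (simulated 0.470).

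The aspect differs by race and predicts the outcome, yet the groups have the same mean outcome. This needs an offsetting direct effect. It is a possibility that the plan cannot detect, not a prediction.

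**4. How precisely could the difference be estimated?**

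The article gives no figure for this comparison; its power statement concerns provider implicit prejudice and communication style. The inputs here are 220 patients, split about 110 and 110 (Participants section), and an assumed ICC of 0.05 to 0.10.

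With balance within providers, SE = 2 × √(1 − ICC)/√220 in SD units.

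- ICC 0.05: 2 × 0.975/14.83 = 0.131.
- ICC 0.10: 2 × 0.949/14.83 = 0.128.

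Ignoring clustering, SE = √(2/110) = 0.135. Two-sided power is then:

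| True d | α = 0.05 | α = 0.01 (Bonferroni over an assumed five outcomes) |
|---|---|---|
| 0.2 | 0.32 | 0.14 |
| 0.3 | 0.60 | 0.36 |
| 0.4 | 0.84 | 0.65 |
| 0.5 | 0.96 | 0.87 |

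Power of 80% is reached at d of about 0.38 (α = 0.05) or 0.46 (α = 0.01).

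**The case against.** The best defence is the filter. Step 2 of Aim 4 uses aspects identified in Aims 1 and 2, and Table 1 defines those aims as finding what differs between Black and White patients. An aspect reaching Step 3 has therefore been linked to race, and Step 3 links it to the outcome. That resembles a joint-significance test of mediation, and the conclusion is hedged, calling the aspects only potentially important. This part stands: the sequence is indirect evidence of contribution. It still yields neither the outcome difference nor the part that runs through communication.

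A second defence is that an article condenses a fuller plan, which might contain a simple outcome-by-race table. But the article itself fixes the path assignment and a closed predictor set for all Aim 4 regressions, and names race in the other three aims. The mismatch is in what is stated.

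A reader might also infer more than the text supports:

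- *That an aspect related to satisfaction equally in both races is wrongly labelled.* No. If the aspect differs by race, an equal slope still carries a difference through to the outcome.
- *That Path G is the total race effect and goes untested.* The Background describes it as the last link of a chain, and Figure 1 is not available here. It can be said only that no aim is assigned to it.
- *That Paths E and F are confounded by race.* This is possible but not established. Aspects chosen because they differ by race should correlate with race, so the Step 1 screen is likely to admit it.
- *That the Aim 4 conclusion has no support at all.* The filter gives it some.

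**Conclusion.** The concern holds as a gap between the stated goal and the specified analysis. None of the stated models estimates the Black-White difference in a patient-centered outcome, and the covariate route does not supply it. This follows from the text and needs no numerical assumption.

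The illustrations use assumed coefficients and show only what the present models cannot distinguish. The standard error of about 0.13 SD assumes an ICC of 0.05 to 0.10, balance within providers (the article says approximately equal), a race gap that does not vary between providers and no missing data. It does not apply to testing completion, which is binary. Because power at d = 0.2 is only about 0.32, a non-significant race difference would not show that there is no disparity.

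The change should be made. It lets the study answer a question that it sets itself, from data already planned.

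**What to change.** In Aim 4, for each patient-centered outcome:

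1. Add a GEE model (linear or logistic, as already planned) on patient race and care modality with pre-specified covariates, without the communication and topic aspects. Include the baseline measure where one exists: the same scale for empowerment, approximate counterparts for trust and satisfaction, and none for alliance or testing completion. Report the race difference with a confidence interval.
2. Force race into the Step 3 models. Report its coefficient with and without the aspects, using an interval method suited to about 15 providers.
3. Do not make the conclusion depend on significance of the race difference. Word it according to the estimate and its interval.

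If the team does not want these models, narrow the overarching goal, the Table 1 goal for Aim 4 and the closing sentence of Aim 4 to associations of communication and discussion topics with patient outcomes.

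The cost is one extra model per outcome and no new data. The drawback is the limited precision shown above: small disparities will come with wide intervals.

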## Discussion

We acknowledge that the role of counselor bias in racial healthcare disparities may be statistically small [27, 30]. However, even statistically small effects can have significant societal impact when a large number of people are affected, [95, 96] as in the case of Black patients interacting with White genetic counselors. We also acknowledge that counselor bias is one of many multilevel determinants of racial disparities. Additionally, individual bias is closely tied to systemic racism [97, 98]. Thus, addressing counselor bias—an individual level factor—is not sufficient to eliminate racial disparities in the genetic counseling process. Yet, structural-level factors, including systemic racism and the effort to diversify genetic counselors, are highly resistant and slow to change, requiring significant time and financial resources. Given the urgency of the current state of racial cancer disparities, it is critical to address modifiable factors that can produce desired outcomes immediately, including counselors’ bias-associated behaviors, while continuing to address structural-level factors.

We emphasize bias-related behaviors, not bias per se, because changing fundamental attitudes and beliefs that are deeply ingrained in our society and have perpetuated systemic racism for centuries [97, 98] is a challenge, requiring considerable investment of time and resources [57, 99–101]. Time and volume constraints in the US healthcare system make it difficult for genetic counselors to use evidence-based strategies to reduce bias (stereotype replacement, counter-stereotypical imaging, individuation) [99, 102]. Our conceptual model highlights patient-provider communication and clinical discussions as the mediators linking counselor bias to patient-centered outcomes, suggesting that a viable alternative approach is to train genetic counselors to better *manage their bias-associated behaviors* during encounters with Black patients [22, 103, 104]. In fact, counselor communication behaviors and clinical discussions are an important target point in future interventions because they are both being taught in genetic counseling programs [105]. Thus, interventions that are designed to help counselors manage their bias-associated behaviors can be delivered using the existing infrastructure, which is both cost-effective and efficient.

Once we identify specific counselor communication behaviors associated with patient-centered outcomes, we can design interventions to help genetic counselors adapt their communication behaviors accordingly. Likewise, once we identify specific clinical discussion topics directly associated with patient-centered outcomes, interventions can be designed to provide genetic counselors with a list of topics that need to be discussed and a list of topics that may be omitted during pre-testing cancer genetic counseling encounters. We are not arguing that changing communication behaviors or clinical discussions is easy; indeed, changing those particular behaviors requires effort and practice. However, communication behaviors and clinical discussions are relatively modifiable, and that is why they are being taught in genetic counseling programs [105]. Indeed, genetic counselors and training programs are heavily invested in improving training in this area. The Accreditation Council for Genetic Counseling (2019) standards state that MS Genetic Counseling curricula must include content related to “multicultural sensitivity and competence.” [106] A recent study found that, 90% of genetic counseling graduate programs provide opportunities for diversity, inclusion, cultural competency, and equity (DICE) training, and 68% require it [11]. Our research will lay the foundation for interventional research to manage counselor bias-associated behaviors and further inform DICE training.

## Data Availability

Not applicable for this protocol paper. Data from the project will be available mainly through presentations at scientific conferences, publications, and speaking engagements.

## Abbreviations

MS: Master of Science
HIPAA: Health Insurance Portability and Accountability Act
QR code: Quick response code
RIAS: Rotor Interaction Analysis System
LIWC: Linguistic Inquiry and Word Count
ICC: Intraclass correlation coefficient
NCI: National Cancer Institute
IAT: Implicit Association Test
BMI: Body mass index
GOS: Genomics Outcomes Scale
ATGT: Attitudes Toward Genetic Testing
DCS: Decisional Conflict Scale
WAI-SR: Working Alliance Inventory-Short Form Revised
GCSS: Genetic Counseling Satisfaction Scale
GEE: Generalized estimating equation
DICE: Diversity, inclusion, cultural competency, and equity
